### Preparation of the intervention

In both intervention and control clinics the project will be presented to healthcare providers.

A healthcare team will implement the intervention comprised of family doctors, two nurses (one for each working shift) and a psychologist. The nurses and the psychologist will be selected from those with clinical experience in providing care to climacteric stage women; they will be previously trained by researchers and will work specifically in this project. The training will include theory and practice, and will last 60 hours based on a "training guide" that was developed *ex profeso*. The training topics include: 1) Health needs of climacteric stage women; 2) Risk factors for chronic diseases during the climacteric stage and self-care-related activities; 3) Health behaviors, self-efficacy, knowledge regarding climacteric stage and health-related self-care activities and empowerment; 4) Cognitive restructuring and problem solving, self-esteem and communication; 5) Healthy diet enriched with fruits, vegetables and milk products; 6) Regular leisure time with physical activity; 7) Individual counseling from the empowerment approach. Self-care plan: goal setting, action planning, monitoring and achievement of health goals; 8) Group counseling from the empowerment; 9) Integrative health care model for women at the climacteric stage.

All family doctors working in the intervention clinic will be invited to participate in the study. Family doctors, who agree to collaborate, will participate in a training course that consists in reviewing and discussing the proposed model, the roles and responsibilities of health providers involved in the care of climacteric stage women within IHCM. The researchers will deliver this course that will last two sessions of 60 minutes each.

### Description of the intervention

The IHCM with an empowerment approach will address the care that should be given collaboratively by the health team in cooperation with the active participation of women. The IHCM will be provided under the leadership of the nurse who will coordinate with the health team members, promote preventive care, and incorporate cognitive-behavioral strategies, such as individual and group counseling. The IHCM will be provided for three months to each woman, followed by a three-month follow-up. The empowerment of women will work to facilitate women's recognition of their actual or potential health problems, enable them to solve these problems by drawing up an action plan to improve or maintain their health, and develop their autonomous health-related self-care skills.

In the control group, women will continue the usual healthcare consisting of curative care provided by their family doctor and preventive care according to the IMSS prevention programs focused on this age group (chronic disease screening) and provided by nurses according to the women's demand.

### Recruitment of women and consultation with the family doctor

In both working shifts (morning and afternoon) family doctors will identify and evaluate those women who meet the inclusion criteria. Family doctors should provide preventive and curative healthcare services, according to womens' individual health needs, and send the candidates to the waiting room where they will be interviewed by study interviewers, who will explain the purpose and content of the study, and obtain the signed informed consent from those women who agree to participate. Once the participant is included in the study, the interviewer will perform the base-line interview then send the woman to the nurse of the study.

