## Methods/Design

A field trial with one intervention and one comparison group, with ex ante and ex post measurements will be conducted in two IMSS primary care clinics in Mexico City. The clinics will be selected for convenience; each clinic must have more than 20 family doctors' offices and available space for the intervention (consulting room and an area for group counseling) and should have accepted to participate in the study; The intervention will be conducted in one clinic and the other clinic will serve as a comparison group, where the usual care for climacteric stage women will be observed.

The study population will consist of women affiliated with IMSS, between 45 and 59 years of age with a maximum of 5 years after menopause. The women should be users of the clinic, and should not have mental conditions that would prevent them from understanding the information or from taking independent decisions (dementia, mental retardation or psychosis), a physical disability that would impede them from participating (hearing loss, diseases affecting physical mobility as severe forms of rheumatoid arthritis), medical diagnosis of depression, diabetes mellitus, hypertension, renal or liver failure, and/or cancer, because patients with these diseases require specific care provided by several specialists. All women must agree to participate in the study through written informed consent.

The project was authorized by the National Research and Ethics Committee of the IMSS.

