### Study variables

The main outcome variables will be:

Health-related quality of life (HR-QoL), which will be measured with the revised version of Women's Health Questionnaire (WHQ23) [43]. This is a specific questionnaire for women in perimenopause, menopause and post menopause stages, that comprises six domains: anxiety/depression, well-being, somatic symptoms, memory/concentration, vasomotor symptoms and sleep problems. The WHQ23 also has two optional domains: sexual behavior and menstrual symptoms, which will apply only to women who are sexually active or who have menstrual periods. The highest value for each domain score is 100, which means high HR-QoL, and the lowest is 0, which means low HR-QoL.

Other outcome variables will be:

1) Empowerment of women in relation to their self-care measured by the empowerment scale, which was modified from the diabetes empowerment short scale [44] to be used in climacteric women. The maximum score of empowerment is 5, the minimum is 1.

2) Self-efficacy of women in relation to menopause and its care will be assessed with Perimenopausal Health Self-efficacy Scale (PHS-ES) which consists of 23 items [45]. The maximum score of PHS-ES is 207 (high self-efficacy) and the minimum is 23 (low self-efficacy).

3) Women's knowledge about the climacteric stage will be estimated with a questionnaire developed *ex profeso*. The questionnaire consists of 24 items that assess the following aspects: what is the climacteric stage, what are climacteric symptoms and health risks, and how can they be prevented during the climacteric stage. The minimum score on the scale corresponds to -24 points (without knowledge) and the maximum 24 points (full knowledge).

4) The use of screening services for: a) breast cancer by mammography in the last two years; b) cervical cancer by Pap-test in the last three years in women without a history of total hysterectomy; c) diabetes by measuring fasting plasma glucose in the last three years; d) hypertension: by measuring the systolic and diastolic blood pressure in the last year. The use of screening services will be estimated as the sum of the number of screening services that women used, divided by the total number of screening services recommended according to IMSS regulations and multiplied by 100.

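### The baseline interview follows the family doctor's consultation, so a screening service completed at that visit is scored as baseline status

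*Protocol article*

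**What the plan says.** Methods/Design describes a field trial "with ex ante and ex post measurements". The section on recruitment and the family-doctor consultation fixes the order of the first visit: "Family doctors should provide preventive and curative healthcare services, according to womens' individual health needs, and send the candidates to the waiting room". Study interviewers explain the study and obtain consent there, and then "the interviewer will perform the base-line interview then send the woman to the nurse of the study".

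The family doctor is part of the model under test. Preparation of the intervention states: "A healthcare team will implement the intervention comprised of family doctors, two nurses (one for each working shift) and a psychologist". Doctors in the intervention clinic who agree to collaborate "will participate in a training course that consists in reviewing and discussing the proposed model", in two one-hour sessions. For the control group, Description of the intervention specifies "usual healthcare consisting of curative care provided by their family doctor and preventive care according to the IMSS prevention programs", with nurses giving the preventive part when women ask for it.

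Study variables defines screening use as the percentage of recommended services that a woman has used. Four are named: mammography within two years, Pap test within three years (not after total hysterectomy), fasting glucose within three years, and, for hypertension, "by measuring the systolic and diastolic blood pressure in the last year". Data collection sets measurements at entry, three months and six months. Statistical analysis compares outcome variables before and after within each group, and between groups with the difference-in-differences (D-in-D) estimator.

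**The concern.** A before-and-after design needs a baseline taken before the care it evaluates. Here the first care from one team member comes before the interview. Most outcomes cannot change in the time it takes to walk to the waiting room, but the screening index can: a blood-pressure reading taken in the consulting room makes that item positive at the interview. Because the look-back is one year, the item is still positive at three and six months, so it cannot improve in that woman.

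Screening use is one of the listed aspects of effectiveness. If services given at the recruiting visit are absorbed into baseline, and more so in the intervention clinic, part of what the model achieves is subtracted from its own estimated effect. The limitations in the Discussion consider that the baseline evaluation may influence control women, but not that model care may influence the baseline.

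**Working it through.** The protocol gives no figure on this point, so there is none to reproduce. The check sets the sections side by side and then bounds the size under stated assumptions.

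**Order of care.** Doctor's care, then consent, then baseline interview, then study nurse. Nurse, psychologist and group counselling all come after baseline; only the doctor's consultation comes before it.

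**Do the clinics differ at that visit?** The recruitment section has family doctors giving both preventive and curative care and sends women on to the study nurse, which is the intervention-clinic flow. The control description gives doctors curative care and leaves prevention to nurses on demand. Only intervention-clinic doctors attend the course on the model. These contrasts suggest a difference without establishing one. The article does not say how the control clinic recruits.

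**Weight of one service.** 100/4 = 25 points; after total hysterectomy, 100/3 = 33.3 points.

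**Notation (all values assumed).** p is the share of women with a blood-pressure reading in the past year before the visit, taken as equal in both clinics. q is the share of the remaining women who are measured at the visit, written qI and qC for the intervention and control clinics.

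- Inflation of a group's mean baseline index = 25 × (1 − p) × q. The follow-up index does not change, because the reading is still inside the one-year window. Within-group change is therefore understated by this amount. With q = 1 it is 25 × 0.6 = 15 points at p = 0.4, 25 × 0.4 = 10 at p = 0.6 and 25 × 0.2 = 5 at p = 0.8.
- Loss in D-in-D = 25 × (1 − p) × (qI − qC).

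| p | qI − qC = 0 | 0.1 | 0.3 | 0.5 |
|---|---|---|---|---|
| 0.4 | 0 | 1.5 | 4.5 | 7.5 |
| 0.6 | 0 | 1.0 | 3.0 | 5.0 |
| 0.8 | 0 | 0.5 | 1.5 | 2.5 |

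For example, 25 × (1 − 0.6) × 0.3 = 3.0 and 25 × (1 − 0.4) × 0.5 = 7.5. The table is for women with four recommended services; for those with three, multiply by 4/3. If qI = qC, the two inflations cancel in D-in-D, whatever their common size. If control doctors measured more, the sign would reverse.

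**Other components and outcomes.** Mammography, Pap test and fasting glucose are more likely to be ordered than completed before the interview, so blood pressure is the main exposed item. Advice given in the consultation might move knowledge, empowerment or self-efficacy scores slightly. Weekly activity minutes, daily diet and the WHQ23 domains should hardly move.

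**The case against.** The strongest case on the other side is that the baseline is *ex ante* to nearly all of the model. The model is nurse-led, and "The IHCM will be provided for three months to each woman, followed by a three-month follow-up"; nurse, psychologist and group contacts come after the interview, as do the nurse's referrals back to the family doctor. The recruiting consultation takes place before consent and according to individual need, so it can be read as the ordinary visit at which eligible women are found. The doctors' two hours of training cover the model and team roles; nothing says they are taught to screen more at that visit. D-in-D removes any shift common to both clinics. The article is condensed, and the questionnaire may already exclude the day's visit.

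Much of this stands, and it limits the point. A reader might infer that the trial's measured effect is reduced in general, HR-QoL included. The documents do not support that: the counselling components follow baseline, the primary and lifestyle outcomes cannot plausibly respond within minutes, and a bias in D-in-D needs a between-clinic difference that the article does not state.

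Three things remain. The order of events is stated, not left out. Equality between clinics cannot be presumed, given how differently the doctor's role is described for the two settings. And the planned within-group comparisons get no protection from cancellation.

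A fair objection also applies to the remedy: services given before consent would be credited to follow-up, so a clinic difference in them that is unrelated to the model would be attributed to it.

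**Conclusion.** The point holds for the screening-use index, chiefly its blood-pressure component. As written, a service completed at the recruiting visit is baseline status. Within-group change in the index is understated by whatever was done at that visit. The D-in-D is biased toward zero if intervention-clinic doctors do more there than control doctors, which the contrasting descriptions of care suggest but do not prove. If the clinics behave alike, only a ceiling on one item remains.

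The size cannot be derived from the documents. Under the assumed ranges (prior coverage 0.4 to 0.8, equal in both clinics; difference in newly measured women 0 to 0.5; four recommended services), the D-in-D loss is 0 to 7.5 points of 100. Slight effects on knowledge, empowerment and self-efficacy are possible. HR-QoL, physical activity and diet are not materially affected, so the primary comparison is not called into question.

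**What to change.** In both clinics, define the baseline screening look-back as ending before the recruiting visit, for instance by asking every baseline screening item as of before today's visit, so that services given at that visit are not scored as baseline. Use the same recruitment sequence in both clinics and say so in the protocol. If the full protocol or questionnaire already does this, a sentence confirming it is enough. Where visit flow allows without withholding care, hold consent and the baseline interview before the consultation; this would also protect the knowledge, empowerment and self-efficacy scores.

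The cost is a small change in question wording or visit flow. The price in interpretation is that services at the recruiting visit are credited to follow-up in both groups, which is why the sequence needs to be the same in both clinics.

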### Individual counseling by nurse

Nurses will provide monthly individual counseling to each woman based on the empowerment approach (the first visit being 40 to 60 minutes with subsequent counseling sessions of 20 to 30 minutes). The individual counseling will include the following contents (Table 2): 1) the nurse and the woman collaboratively evaluating the current status of the participant (physical, emotional, cognitive and so forth) within their social environment; 2) the nurse facilitating the women's recognition of her personal health risks and responsibilities for health-related self-care; 3) and 4) the nurse guiding the woman in setting her health goals and laying out a feasible action plan for her health-related self-care, thereby promoting the empowerment of each participant; and 5) the nurse and the woman collaboratively monitoring the progress of the action plan.

**Table 2 T2:** Individual counseling for climacteric stage women

Steps	Content
1) Evaluation of the current status of women (physical, emotional, cognitive, etc.) within their social environment	• The nurse and the woman collaboratively assess the woman's health and health-related self-care practices (diet, leisure time physical activity, use of screening services).
	• The nurse provides relevant information on climacteric self-care: a) explains the definition of the climacteric stage and menopause and health problems the woman may experience during and after the climacteric stage; b) describe the factors (activities) that cause or protect against the occurrence of such problems; c) answers the woman's questions.
2) Facilitation of the woman's recognition of her personal health risks and responsibility for health-related self-care	• The nurse guides women on specific personal health-related values, beginning with the question: What health would you like to have in the next 10 years?
3 and 4) Guidance on the health-related goal setting and elaboration of a feasible action plan for women's self-care	• The nurse guides women to choose their personal health-related self-care goals.
	• The nurse guides women to choose strategies/actions to overcome barriers, using the problem-solving model.
	• The nurse facilitates the agreement of women to carry out the action plan.
	• The nurse and women jointly assess the level of womens' self-efficacy regarding the achievement of the agreed actions (on a scale of 0 to 10).
5) Monitoring of the progress of the action plan	The nurse and women jointly:
	• Evaluate progress in achieving the health-related goals and specific actions for development and maintenance of healthy behaviors.
	• Resolve problems related to barriers for implementing the action plan, translating such barriers in the "learned lessons."

Modified from Funnell MM, 2004 to counsel women at the climacteric stage.

The nurse will also schedule appointments for individual and group counseling and refer the woman to the psychologist and to the family doctor, who will provide comprehensive and continuous care consistent with the personal health needs of each participant.

### Individual counseling by the psychologist

Psychological counseling will be based on the Rational Emotive Behavioral Therapy and its central concept ABC [42]. According to this concept, emotional and behavioral consequences (C) are the result of beliefs (B) on activating events (A). The psychologist and the woman will collaboratively evaluate and restructure the woman's erroneous beliefs about the climacteric stage and her emotional resources, which refer to the ability to positively guide the emotions to achieve a better level of self-esteem and self-efficacy. The psychologist and the woman will define the number of consultations required in accordance to her individual needs and characteristics.

### Group counseling

All women of the intervention group will be invited to eight weekly, 90-minutes group sessions to facilitate and enhance their knowledge about menopause and their care, as well as to share experiences, concerns and motivations, with other women. Each group session will be coordinated by the nurse or psychologist of the study and will include five to ten women. The group sessions will focus on common educational needs. Both individual and group counseling will be supported by printed material developed *ex profeso*, which participants will be encouraged to keep as a source of information.

The main themes of group sessions will be: 1) the climacteric stage and the empowerment approach; 2) Emotional well-being, self-esteem and self-efficacy during menopause; 3) Factors that predispose chronic disease development during the climacteric stage and health-related self-care strategies; 4) Physical activity: barriers, benefits, type, frequency and recommended time. How to establish an individual action plan on physical activity and make it feasible (problem solving); 5) Healthy diet during the climacteric stage including increase of intake of fruits, vegetables and dairy products on a daily basis, as well as education about the barriers to and benefits of a healthy diet. How to establish an individual action plan toward a healthy diet and make it feasible; 6-8) Monitoring of the progress of women's action plans. Participants should attend to group sessions one to five, and to sessions six to eight can attend either as a group or individually.

### Data collection

Information on the study variables will be collected on three occasions: when the woman enters to the study (baseline), once intervention is complete (at three months) and after three more months of follow-up (six months).

### Study variables

The main outcome variables will be:

Health-related quality of life (HR-QoL), which will be measured with the revised version of Women's Health Questionnaire (WHQ23) [43]. This is a specific questionnaire for women in perimenopause, menopause and post menopause stages, that comprises six domains: anxiety/depression, well-being, somatic symptoms, memory/concentration, vasomotor symptoms and sleep problems. The WHQ23 also has two optional domains: sexual behavior and menstrual symptoms, which will apply only to women who are sexually active or who have menstrual periods. The highest value for each domain score is 100, which means high HR-QoL, and the lowest is 0, which means low HR-QoL.

Other outcome variables will be:

1) Empowerment of women in relation to their self-care measured by the empowerment scale, which was modified from the diabetes empowerment short scale [44] to be used in climacteric women. The maximum score of empowerment is 5, the minimum is 1.

2) Self-efficacy of women in relation to menopause and its care will be assessed with Perimenopausal Health Self-efficacy Scale (PHS-ES) which consists of 23 items [45]. The maximum score of PHS-ES is 207 (high self-efficacy) and the minimum is 23 (low self-efficacy).

3) Women's knowledge about the climacteric stage will be estimated with a questionnaire developed *ex profeso*. The questionnaire consists of 24 items that assess the following aspects: what is the climacteric stage, what are climacteric symptoms and health risks, and how can they be prevented during the climacteric stage. The minimum score on the scale corresponds to -24 points (without knowledge) and the maximum 24 points (full knowledge).

4) The use of screening services for: a) breast cancer by mammography in the last two years; b) cervical cancer by Pap-test in the last three years in women without a history of total hysterectomy; c) diabetes by measuring fasting plasma glucose in the last three years; d) hypertension: by measuring the systolic and diastolic blood pressure in the last year. The use of screening services will be estimated as the sum of the number of screening services that women used, divided by the total number of screening services recommended according to IMSS regulations and multiplied by 100.

5) Percentage of women who practice regular leisure time physical activity (PA), where regular was defined as moderate intensity if done for ≥150 minutes/week or vigorous intensity if done ≥75 minutes/week.

6) Percentage of women who practice a healthy diet, which included the daily consumption of fruits (3-4 servings), vegetables (4-5 servings), and dairy products (2-3 servings).

The covariates will be:

a) Women's general characteristics: Age, schooling, marital and employment status.

b) Smoking status and alcohol consumption. Smoking status will consider former and current smokers and will register the number of cigarettes actually smoked per day. Alcohol consumption will be classified as non-drinkers (never drink alcohol), occasional drinkers (drink rarely or less than once a week), moderate drinkers (from 1 to 14 drinks per week) and heavy drinkers (more than 14 drinks per week).

c) Nutritional status will be measured by body mass index (BMI) and classified into groups of normal weight (BMI of 18.5-24.9 kg/m^2^), overweight (BMI of 25.0 to 29.9 kg/m^2^), or obese (BMI ≥30.0 kg/m^2^).

d) Social support (SS) will be measured by applying the DUKE-UNC-11 questionnaire [46]. This questionnaire evaluates confidential SS (possibility of having people to communicate with) with a minimum score of 7 points (low confidential SS) and a maximum score of 35 points (high confidential SS); and affective SS (demonstration of love, affection, and empathy) with a minimum score of 4 (low affective SS) and a maximum score of 20 points (high affective SS).

e) Medical and reproductive history: Presence of chronic diseases, number of pregnancies and living children, and menopause (one year after the last menstrual period). Type of menopause will be classified as natural or surgical, age at onset of menopause; time elapsed since menopause, presence and type of climacteric symptoms, and number of visits with the family doctor or other health provider in the last three months. The severity of vasomotor symptoms and vaginal atrophy symptoms is classified using the criteria proposed by the Department of Health and Human Services Food and Drug Administration [47], which are based upon women's self-report, and define the symptoms as mild, moderate, or severe.

f) Satisfaction with care received at the FMC will be measured with the general question of how satisfied are you with the care you have received at the clinic? The possible answers are very satisfied, satisfied, neither satisfied nor unsatisfied, unsatisfied, and very unsatisfied.

g) Women's self-esteem will be measured with the Rosenberg Self-Esteem Scale (EAR) [48,49]. It is a one-domain instrument that consists of 10 questions. The highest score is 30 (high self-esteem) and the lowest is 0 (low self-esteem).

h) Adherence to MAIMC will be defined when the woman attends at least 60% of the planned individual and group counseling sessions.

